### Recruitment {15}

This trial will recruit participants from the joint study sites listed above. IVFHK-CUHK has extensive experience in conducting large-scale clinical trials, including a published international multi-center RCT on embryo time-lapse imaging [16]. The study has enhanced recruitment strategies and operational efficiency at both centers. With a strong infrastructure and prior success in participant enrollment, this trial is well-positioned to achieve the target sample size efficiently.

## Assignment of interventions: allocation

### Sequence generation {16a}

A stratified randomization approach will be used to ensure balanced distribution of participants across treatment groups based on age, a key factor influencing embryo warming and transfer outcomes. Participants will be stratified into two age groups: ≤35 years and >35 years.

Within each age stratum, participants will be randomly assigned to one of two study groups (conventional warming or direct warming) using a computerized randomization process in sealedenvelope.com. Random numbers will be generated for each participant, and participants will be assigned to the intervention or control group randomly, ensuring even distribution across groups within each age stratum.

In the case of an odd number of participants in any stratum, the remaining participant will be randomly assigned to one of the two groups. This method ensures that participants are randomized within each stratum, achieving a balance in age distribution across the treatment groups.

### Concealment mechanism {16b}

The allocation sequence will be concealed using a sequentially numbered, opaque, sealed envelope system. After stratified randomization has been conducted in sealedenvelope.com, each participant’s group assignment will be placed in a numbered, opaque envelope. These envelopes will be prepared in advance and will only be opened by the embryologist responsible for embryo handling. The research staff/nurse/clinician responsible for enrolling participants will not be aware of group assignments, ensuring allocation concealment until the interventions are carried out.

After the embryo transfer, if it is determined that the patient is not pregnant, their group assignment may be disclosed to them. However, if pregnancy is confirmed, the group assignment will remain concealed, and the patient will not be informed until a live birth occurs, or in the event of a miscarriage or elective termination. This approach ensures allocation concealment throughout the pregnancy, minimizing bias and maintaining the integrity of the trial.

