### Eligibility criteria {10}

#### Inclusion criteria

Participants will be eligible for inclusion in this study if they meet the following criteria:Patients undergoing a FET cycle at one of the study centers.Plan to undergo single embryo transfer (SET) during the FET cycle.Age between 18 and 45 years.Patients with at least one good-quality blastocyst suitable for transfer.Patients who have provided informed consent to participate in the study.

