### Intervention description {11a}

Intervention group (arm 1): new direct warming methodIn the intervention group, vitrified blastocysts will be thawed using a novel direct warming method. The ready-to-be-thawed blastocyst is placed in a pre-warmed direct warming medium for 1 min. Following this, the embryo is transferred directly into the embryo culture medium in a time-lapse system until it is ready for transfer into the uterus. This new warming method significantly reduces the procedure time to approximately 3 min, making it much faster than the conventional multi-step warming process.Control group (arm 2): conventional multi-step warming methodThe control group will follow the conventional multi-step warming method. In this procedure, vitrified embryos are first placed in a pre-warmed thawing solution for 1–3 min. They are then transferred to a dilution solution for 4–6 min to gradually dilute the cryoprotectants, followed by immersion in a washing solution for 5–10 min to complete the rehydration process. This multi-step method takes approximately 20 min to complete. After thawing, the embryos are placed in the embryo culture medium in a time-lapse system until they are ready for transfer.Blastocysts will be evaluated using the Gardner grading scale with a three-part criterion on blastocyst expansion, inner cell mass (ICM), and trophectoderm (TE) quality. Blastocysts with a score ≥3BB are considered good quality [13].

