### Implementation {16c}

The research staff will be responsible for enrolling participants. After participants are enrolled, each participant’s group assignment will be determined by opening a sequentially numbered, opaque, sealed envelope, which will have been prepared in advance by the research staff following the randomization process. The envelopes will only be opened after baseline data collection is complete to ensure allocation concealment.

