## Assignment of interventions: blinding

### Who will be blinded {17a}

This trial will be conducted as a double-blinded study. Both the trial participants and the clinical team will be blinded to the group assignments after the allocation to interventions has been completed. Neither group will have access to information about whether participants are in the intervention group (direct warming method) or the control group (conventional warming method).

Outcome assessors will also be blinded to the group assignments to ensure unbiased evaluation of primary and secondary outcomes, including embryo survival rates, pregnancy rates, and live birth rates. Data analysts will be blinded to the group allocation during the analysis phase to prevent bias in data interpretation.

The use of sequentially numbered, opaque, sealed envelopes ensures allocation concealment until the point of intervention, maintaining blinding throughout the trial.

Embryologists cannot be blinded in this trial.

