## Data collection and management

### Plans for assessment and collection of outcomes {18a}

The assessment and collection of outcomes, baseline, and other trial data will follow standardized procedures to ensure accuracy and consistency. The primary and secondary outcomes, including pregnancy rates, live birth rates, and embryo survival rates, will be assessed through clinical evaluations, ultrasound examinations, and laboratory testing.

Baseline data will be collected at the time of enrollment, including participants’ age, fertility history, and any relevant medical conditions. These data will be collected using structured case report forms (CRFs), designed to minimize errors and ensure consistency across participants. The CRFs will be attached as part of the study protocol for reference.

Study instruments, such as ultrasound machines for clinical pregnancy assessment and standardized laboratory assays for hCG measurements, will be used. These instruments have been validated for reliability and accuracy in clinical settings.

All data will be recorded in a secure, encrypted electronic database. Regular data audits will be performed to ensure completeness and accuracy.

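### The rule for opening the allocation envelope does not require the blastocyst to be named first, so the unblinded embryologist may choose or replace the embryo knowing the arm

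*Protocol article*

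**What the plan says.** Five statements in the protocol article bear on this point.

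- **Who opens the envelope** (Concealment mechanism {16b}): the envelopes "will only be opened by the embryologist responsible for embryo handling".
- **Blinding of that person** (Who will be blinded {17a}): "Embryologists cannot be blinded in this trial".
- **When it may be opened** (Implementation {16c}): "The envelopes will only be opened after baseline data collection is complete to ensure allocation concealment".
- **What baseline data are** (Plans for assessment and collection of outcomes {18a}): "Baseline data will be collected at the time of enrollment, including participants’ age, fertility history, and any relevant medical conditions".
- **Which embryos are eligible** (Inclusion criteria; Intervention description {11a}): "Patients with at least one good-quality blastocyst suitable for transfer", together with "Plan to undergo single embryo transfer (SET) during the FET cycle" and the threshold "Blastocysts with a score ≥3BB are considered good quality".

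Table 1 places allocation at week 0, in a column before the embryo transfer column, which is where warming is marked. It has no row for choosing the embryo. The article does not say who picks the blastocyst, by what ranking or at what moment, or what follows if a warmed blastocyst does not survive.

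**The concern.** The woman is randomised, but the treatment acts on one blastocyst. If she has several, the choice among them affects her chance of pregnancy and live birth. The opening condition protects recruitment, because enrolling staff do not know the next assignment. It does not protect the choice of embryo, because the person who learns the arm is the person who handles the embryos.

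Two routes to bias follow. An embryologist who doubts the new method could keep the best blastocyst back from it, and one who favours it could do the reverse. Separately, if a further blastocyst were warmed after a poor first result, a survival loss in one arm could be hidden in the per-woman pregnancy and live birth rates. The denominator for embryo survival would also be unclear. Survival matters here: Statistical methods {20a} names it among the primary outcomes, and Interim analyses {21b} uses it as the example of a stopping criterion.

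**Working it through.** The plan gives no figure on this point to reproduce. The check sets the statements side by side and then scales the possible effect on stated assumptions.

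**1. Is there a choice to make?** Eligibility needs one or more blastocysts at or above the grade threshold, and one is to be transferred. Women with two or more candidates are eligible, and their candidates may differ in grade. The share with only one is not given; those women are not exposed to selection.

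**2. Does any stated step fix the embryo before opening?** The condition in {16c} is completed baseline data. The list in {18a} names no embryo item, though it is not exhaustive. The eligibility screen comes before allocation in Table 1, so the grade of at least one blastocyst must be known by then. Knowing that a suitable blastocyst exists does not name the one to be warmed. A site can meet every stated condition, open the envelope and then pick the straw.

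**3. Does replacement depend on that order?** No. Once a blastocyst has been warmed, the embryologist knows the method used. Any further choice is made with the arm known, whenever the first choice was made.

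**4. Do the other safeguards close the gap?**
- Adjustment for embryo quality ({20a}) and grading ({20b}) addresses differences between grades. It misses choice within a grade. If the embryo is chosen after opening, its grade is a post-randomisation variable.
- The warming record and audits ({11c}) capture the steps and deviations, but a choice that breaks no rule is not a deviation.
- Intention-to-treat analysis keeps women in their arm, and blinding of participants, clinicians, assessors and analysts does not reach the bench. Neither undoes an arm-dependent choice.

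**5. Illustration of size (inputs assumed, not from the document).** Let *f* be the share of women in one arm whose embryo choice is changed by knowing the arm, all in one direction, and *g* the resulting difference in live birth chance. Then bias = *f* × *g*.

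For the effect on a test with no true difference, take 275 per arm (Sample size {14}), an assumed control live birth rate *p* of 30-50% and a two-sided 5% level:

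δ = bias / √(2*p*(1−*p*)/275); type I error = 1 − Φ(1.96 − δ) + Φ(−1.96 − δ).

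Example with *p* = 0.30 and bias 0.02: standard error = √(2 × 0.30 × 0.70/275) = 0.0391; δ = 0.51; type I error = 0.0805.

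| *f* | *g* (points) | Bias (points) | Share of a 5-point gain | Type I error, *p* = 30-50% |
|---|---|---|---|---|
| 10% | 5 | 0.5 | 10% | 0.052 |
| 10% | 10 | 1.0 | 20% | 0.056-0.058 |
| 20% | 10 | 2.0 | 40% | 0.076-0.081 |
| 30% | 10 | 3.0 | 60% | 0.108-0.120 |
| 30% | 15 | 4.5 | 90% | 0.18-0.21 |

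The 5-point reference is the roughly 5% live birth increase in {14}, read as percentage points.

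**The case against.** The strongest reply is that the order of events is inferred from silence. {16b} and {17a} say that concealment lasts until the intervention, and {11a} starts the direct warming arm with an embryo already in hand: "The ready-to-be-thawed blastocyst is placed in a pre-warmed direct warming medium for 1 min". Both fit a blastocyst chosen before the envelope is opened. Table 1 is too coarse to settle the order. This stands: a reader might infer that embryos will be chosen with the arm known, and the document does not say so. Equally, it does not rule it out.

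A second reply is that a journal article leaves straw identification and laboratory ranking to the full protocol, the case report forms or site procedures. That has force for laboratory detail. But the article does state an opening condition, and that condition does not cover the embryo. The point concerns the stated rule rather than an absent one.

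Third, a reader might infer that embryo grade is left out of the baseline data. That goes too far: the list is open-ended, and grade must be recorded to serve as a covariate and a subgroup factor. What is missing is a requirement to name the chosen embryo before opening.

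Fourth, the illustrated bias is assumed throughout. The upper end needs every changed choice to run the same way, whereas embryologists with opposite leanings would partly cancel. Warming a second blastocyst is also hypothetical, since the article neither describes nor forbids it. All of this stands, and it limits the claim to a possible bias.

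**Conclusion.** The point holds as an avoidable weakness in the allocation procedure, not as a demonstrated bias. The stated rule lets the unblinded embryologist open the allocation without first naming the blastocyst, and it leaves any replacement to be made with the arm known. The existing adjustment, records and audits reduce the exposure but do not remove it.

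The 0.5-4.5 point range should not be read as an estimate. It rests on assumed values of *f* and *g*, on all changes running in one direction within one arm, and on enough women having more than one blastocyst. The document supports no figure for size and none for direction. It matters because the upper part of that range is close to the live birth gain the protocol cites, while closing the gap costs very little. It should be changed, as a cheap improvement; the sample size of 578 is not affected.

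**What to change.** In {16b} and {16c}, make opening the envelope conditional on a written record of:

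- the straw ID and pre-vitrification grade of the blastocyst to be warmed;
- the rank order of any back-up blastocysts.

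Then state in the analysis sections that:

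- embryo survival is counted on the first-listed blastocyst of each randomised woman;
- the grade recorded before opening is the embryo-quality covariate and subgroup variable;
- any departure from the recorded choice, and any use of a back-up, is logged and reported by arm.

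Whether a back-up is warmed stays a clinical decision; the change only makes its use visible.

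The cost is a wording change and one more line on the warming record that {11c} already requires, with slightly less flexibility on the day. No extra participants or procedures are needed. If the full protocol or a laboratory procedure already fixes the embryo before opening, a sentence saying so in {16c} would settle the selection part; the handling of replacements would still need stating. The change protects only women randomised after it is made, because the moment of choice cannot be reconstructed reliably later.

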**Fig. 1 Fig1:**
[figure not shown]
RCT flowchart

**Table 1 Tab1:** Schedule of the study process

Timepoint	Study period							
	Enrollment	Allocation	Post-allocation					Close-out
	IVF talk	0 week	Embryo transfer	10–14 days	6–8 weeks	20–24 weeks	36–40 weeks	6–8 weeks after birth
Enrollment								
Eligibility screen	X							
Informed consent	X							
Allocation		X						
Interventions								
Administration of different embryo warming methods			X					
Assessments								
Post-thaw embryo assessment			X					
HCG test				X				
Ultrasound of gestation					X			
Phone follow-up						X	X	X

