### Plans to promote participant retention and complete follow-up {18b}

To promote participant retention and ensure complete follow-up, the research team will maintain regular contact with participants through phone calls. Participants will be scheduled for follow-up assessments at specific time points post-embryo transfer, including hCG testing 2 weeks after transfer, ultrasound at 6–8 weeks gestation, and follow-up on pregnancy outcomes such as live birth and birth abnormalities.

For participants who discontinue or deviate from the intervention protocols, efforts will be made to collect all relevant outcome data up until the point of withdrawal. This will include:Reason for discontinuation: collected through phone interviews or in-person discussions.Pregnancy outcomes (if applicable): including any positive or negative pregnancy tests, clinical pregnancy, and live birth outcomes, if the participant is still willing to provide this information.

In cases where participants cannot complete the entire follow-up protocol, efforts will be made to collect as much data as possible from medical records.

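### Allocation may be disclosed from live birth, 6–8 weeks before the only scheduled post-birth contact, so some mothers may be unblinded when post-birth safety information is collected

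*Protocol article*

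**What the plan says.** Concealment mechanism {16b} sets two disclosure rules. For a failed transfer, "if it is determined that the patient is not pregnant, their group assignment may be disclosed to them". For a confirmed pregnancy, "the patient will not be informed until a live birth occurs, or in the event of a miscarriage or elective termination". The section sums up its own scope this way: "This approach ensures allocation concealment throughout the pregnancy".

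Table 1 (Participant timeline {13}) marks "Phone follow-up" at three points: 20–24 weeks, 36–40 weeks, and close-out at "6–8 weeks after birth". Only the last is defined as after birth.

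The retention plan {18b} says that "the research team will maintain regular contact with participants through phone calls" and lists among the assessments "follow-up on pregnancy outcomes such as live birth and birth abnormalities". It mentions medical records for participants who cannot complete follow-up.

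On blinding, {17a} says that participants are blinded, gives no end to that state, and describes the sealed envelopes as "maintaining blinding throughout the trial". The unblinding procedure {17b} allows an allocation to be revealed for participant safety or to guide care after a serious adverse event, and otherwise excludes routine disclosure.

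**The concern.** Disclosure and the last data collection are in the wrong order. The event that releases the allocation, a live birth, comes before the one scheduled contact at which information about the child can be gathered. A mother who knows that her embryo was warmed by the new method may notice, remember or mention infant problems differently from one who does not, and she may reveal her allocation to the caller. Either could distort the comparison of post-birth safety information, in either direction.

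This information has some weight. Trial design {8} says that the trial compares safety as well as efficacy, and the adverse event section {22} accepts events reported spontaneously by participants. No data monitoring or endpoint adjudication committee is planned; adjudication is left to the study team and the steering committee as needed.

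The text also conflicts with itself. {16b} permits disclosure for reasons other than safety, {17b} excludes it, and {17a} describes participant blinding without a limit.

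**Working it through.** The plan gives no figure on this point to reproduce. The check compares the sections and the timing.

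**1. Timing.**
- Earliest permitted disclosure after a live birth ({16b}): the birth, week 0.
- Only contact defined as after birth (Table 1): weeks 6–8.
- Gap = (6 to 8) − 0 = 6 to 8 weeks in which a mother may be unblinded before the last data collection.

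**2. Outcomes still open when disclosure becomes possible.**
- Clinical and ongoing pregnancy (Outcomes {12}) rest on ultrasound in early pregnancy, so they are settled.
- Miscarriage and live birth are settled by the event that releases the allocation.
- Cost and time measures come from the warming procedure, so they are settled.
- The secondary outcomes compare media and devices on embryo survival, re-expansion, implantation, development and clinical outcomes. Nothing there is defined as a measure taken on the child after birth.
- Birth abnormalities appear in {18b} but not among the primary or secondary outcomes. They, and any adverse event reported after birth, are what remains open.

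**3. Consistency of the blinding statements.**

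| Section | Participant blinding |
|---|---|
| {16b} | ends at live birth, miscarriage, termination or a failed transfer |
| {17a} | stated with no end |
| {17b} | no routine revealing except for safety |

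The first row cannot hold together with the third as written. The second can be reconciled with the first only by adding the limit that it lacks.

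**4. Scale.** Sample size {14} enrolls 289 per arm. The document states neither an absolute live birth rate nor an abnormality rate. For illustration only, assume live birth rates of 30% to 50% and abnormality reports in 3% to 5% of births:
- births per arm: 289 × 0.30 = 86.7 to 289 × 0.50 = 144.5;
- expected reports per arm: 86.7 × 0.03 = 2.6 to 144.5 × 0.05 = 7.2.

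The first line is the number of women per arm to whom the rule could apply; the second shows that the counts would be small. Neither gives the size of a bias. That would need the share of mothers actually told before the call and the effect of knowing on reporting, and the document gives neither.

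**The case against.** The strongest reply is that no declared outcome is touched. Birth abnormalities are not a primary or secondary outcome, and the statistical methods section {20a} names no analysis of them. This stands, and it limits the point to safety follow-up. A reader might infer that the efficacy comparison is biased; the document does not support that, because those outcomes are fixed before disclosure is allowed.

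Second, {16b} sets an earliest time for disclosure and does not order disclosure at birth. With no contact scheduled between birth and close-out, the team may often first learn of the birth at the close-out call. Earlier disclosure would need an unscheduled contact, or a 36–40 week call that happens to follow an early delivery. This also stands: a reader might infer that abnormalities will be reported by unblinded mothers, but the text supports only that some may be.

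Third, the article does not say who supplies the abnormality data. That the mother does so by phone is a reasonable inference from {18b}, not a stated fact; the assessment plan {18a} also mentions clinical evaluations, and the case report forms are not shown.

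Fourth, the promise of blinded assessors in {17a} is tied to the primary and secondary outcomes. A reader might infer that it is directly broken; it is not. An informant revealing her allocation to the caller is a practical risk.

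Fifth, the Discussion's remark on long-term follow-up of birth outcomes reads more naturally as a call for later work than as a safety endpoint of this trial. The point does not depend on it.

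None of this removes the order of events or the conflict between {16b} and {17b}.

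**Conclusion.** The point holds in a limited form. Disclosure is permitted up to 6–8 weeks before the only scheduled post-birth contact, follow-up includes birth abnormalities, and the sections on concealment, blinding and unblinding do not agree. Some mothers may be unblinded when post-birth safety information is collected; how many cannot be known from the document.

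The effect of this cannot be sized. A reader might infer a false risk ratio of 1.5 to 2 from assuming that knowledge of the new method raises reporting by that factor, but such a figure only restates the assumption. With only about 3 to 7 reports per arm under the illustrative rates above, a comparison would be imprecise even if fully blinded.

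The conclusion rests on two readings: that the close-out call is where birth abnormalities are normally recorded, and that the mother is normally the source. Both are plausible but not stated. The conflict in wording rests on neither. This is a cheap improvement, not a threat to the main results.

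**What to change.** In {16b}, for participants with a live birth, replace the release at birth with release once the follow-up at 6–8 weeks after birth has been completed and entered. State that the person making the close-out call has no access to the allocation.

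Then align the other two sections. {17a} should say when participant blinding ends. {17b} should recognize the planned disclosures in {16b} as a stated exception, separate from unblinding for safety, which is unaffected.

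The cost is a few sentences in the protocol and, where the consent information mentions disclosure, a matching line there. Mothers learn their allocation 6–8 weeks later. According to Trial status, recruitment is planned to run until October 31, 2028, so an early amendment would still cover later births.
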